#### Statistical Analysis of the Secondary Outcomes

The lesion complete response rate at 6 months will be processed using the same statistical analysis as the lesion complete response rate at 3 months (previous paragraph). The differences in pain scores at the end of treatment between P-PDT and C-PDT will be assessed using a linear mixed model, with patients as random effects (the significance level will be set at a 2-sided alpha level of 5%). The cosmetic outcomes at 3 and 6 months and the DLQI scores throughout the study will be compared between C-PDT and P-PDT using the Wilcoxon signed-rank test.

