**Methods:**

In this randomized, controlled, multicenter, intra-individual, phase II noninferiority clinical study, subjects with AK of the forehead and scalp are treated with P-PDT on one area and with C-PDT on the contralateral area. In both areas, lesions are prepared and methyl aminolevulinate (MAL) is applied. Thirty minutes after MAL application, the P-PDT area is exposed to red light at low irradiance (1.3 mW/cm^2^) for 2.5 hours so that a light dose of 12 J/cm^2^ is achieved. In the control area (C-PDT area), a 37 J/cm^2^ red light irradiation is performed 3 hours after MAL application. Recurrent AK at 3 months is retreated. The primary end point is the lesion complete response rate at 3 months. Secondary end points include pain scores at 1 day, local tolerance at 7 days, lesion complete response rate at 6 months, cosmetic outcome at 3 and 6 months, and patient-reported quality of life and satisfaction throughout the study. A total of 45 patients needs to be recruited.

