### Study Schema

The study flowchart is shown in Table 1. After screening, patients entering the study had to come to the investigational site for 1 treatment visit (V1) and 3 evaluation visits (V2, V3, and V4). In case of recurrent AK at the 3-month evaluation visit (V3), patients had a second treatment visit within the 3 following weeks (V3bis).

**Table 1 table1:** Study flowchart.

Time point	From day 30 to day 1	Day 1	Day 7±1 day	Months 3±7 days	Day 111±7 days	Months 6±7 days
Visit denomination	Screening	V1	V2	V3	V3bis in case of recurrent AK^a^	V4
Visit type	Screening	Treatment	Evaluation	Evaluation	Treatment	Evaluation
Informed consent	✓^b^	—^c^	—	—	—	—
Medical history	✓	—	—	—	—	—
Check of inclusion and exclusion criteria	✓	—	—	—	—	—
Documentation of AK including location, number, and grade	—	✓	—	✓	✓	✓
Photo-documentation of AK	—	✓	✓	✓	✓	✓
Separation of AK in 2 areas	—	✓	—	—	—	—
Randomization	—	✓	—	—	—	—
Pain score during treatment	—	✓	—	—	✓	—
Adverse effects/reactions	—	—	✓	—	—	—
Skin appearance/cosmetic outcome	—	—	—	✓	—	✓
Completion of the Dermatology Life Quality Index	—	✓	✓	✓	✓	✓
Completion of the satisfaction questionnaire	—	✓	✓	✓	✓	✓
Documentation of adverse events and serious adverse events	—	✓	—	✓	✓	✓
Pregnancy test	✓	✓	✓	✓	✓	✓

^a^AK: actinic keratosis.

^b^Indicates during which visits the actions reported in the first column were performed.

^c^Indicates that the corresponding action was not performed at the considered visit.

On the day of treatment (V1), 10 to 14 AK were located, graded, photographed, and divided into 2 areas (area A and area B) similar to each other in terms of number and grade of AK. The location of each AK was marked on plastic sheets. Randomization was then performed by opening the next envelope in sequence. This envelope specified the protocol that each area had to receive: either P-PDT for area A and C-PDT for area B or C-PDT for area A and P-PDT for area B. In both cases, P-PDT (30-min MAL incubation followed by 2.5 hours of irradiation) was performed first, so that the 3-hour MAL incubation required for C-PDT was achieved after P-PDT was completed.

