Both the areas were prepared by removing crusts, gently scraping the lesion surface, and applying MAL cream (Metvixia, Galderma, France) under a transparent occlusive dressing (Tegaderm, 3M, London Ontario, Canada) to the AK and surrounding normal skin (5-10 mm margin). An aluminum foil was placed over the transparent occlusive dressing, which covered the area randomized to receive C-PDT. The device involved in P-PDT was immediately set up and turned on. After 3 hours, P-PDT was completed as described in the Phosistos Protocol section. The device involved in P-PDT was removed, and the MAL cream was washed off with saline solution. The patient rated his pain on a pain scale. The area that just received P-PDT was then protected with aluminum foil, whereas an Aktilite CL128 lamp (Galderma SA, Lausanne, Switzerland) was placed 5 to 8 cm away from the other area and programmed to deliver 37 J/cm^2^ in 7 to 10 min. At the end of C-PDT, the corresponding pain level was rated by the patient, who also completed the DLQI and the satisfaction questionnaire.

A total of 7 days after the treatment day (V2), patients were invited to report adverse effects/reactions and to complete the DLQI and the satisfaction questionnaire.

The treatment response was assessed 3 months after the treatment (V3) by the investigators by comparison with the photographs at the treatment day (V1). An investigator’s assessment of the skin appearance followed by the determination of the resulting cosmetic outcome was also performed. The DLQI and the satisfaction questionnaire were completed by patients. In case of recurrent AK, these latter were counted, graded, and photographed, and a second treatment visit, identical to the above-described first treatment (V1), was scheduled within 3 weeks after V3 (V3bis).

The last follow-up visit (V4) was performed 6 months after V1. During this visit, the treatment response and the cosmetic outcome were investigator-assessed by comparison with the photographs and the skin appearance at V1, respectively. The patients were asked to complete the DLQI and the satisfaction questionnaire.

Note that any AK appearing between V1 and V4 was not included in the assessment of the study outcomes.

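### The planned paired DLQI comparison between C-PDT and P-PDT has no pairs as the data collection is described: each patient receives both protocols at one visit and completes the DLQI as a whole person

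*Protocol article*

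**What the plan says.** The design is intra-individual. In the Abstract (Methods), "subjects with AK of the forehead and scalp are treated with P-PDT on one area and with C-PDT on the contralateral area". Study Schema adds that both are given at the treatment visit, in a fixed order: P-PDT "was performed first, so that the 3-hour MAL incubation required for C-PDT was achieved after P-PDT was completed".

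Study Schema then sets out what the patient reports at V1. After P-PDT: "The patient rated his pain on a pain scale". After the second protocol: "At the end of C-PDT, the corresponding pain level was rated by the patient, who also completed the DLQI and the satisfaction questionnaire". At V2, "patients were invited to report adverse effects/reactions and to complete the DLQI and the satisfaction questionnaire". At V3, "The DLQI and the satisfaction questionnaire were completed by patients". At V4, "The patients were asked to complete the DLQI and the satisfaction questionnaire". The retreatment visit V3bis is described as the same as V1, and Table 1 also schedules the DLQI there.

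Study Objectives/Outcomes lists the patient's quality of life as a secondary objective, with the DLQI as its outcome, and defines no version for each area or protocol. Statistical Analysis of the Secondary Outcomes states that "the DLQI scores throughout the study will be compared between C-PDT and P-PDT using the Wilcoxon signed-rank test". The same sentence applies this test to the cosmetic outcomes at 3 and 6 months.

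**The concern.** A within-patient design supports paired tests only for outcomes recorded separately under each treatment. Lesion response, pain and cosmetic outcome can be recorded that way. A questionnaire about the patient's life, answered after both treatments, cannot be split between them unless it was built to do so. The article names a paired test, two arms and an outcome, but the data collection it describes does not supply the two scores.

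This is the only analysis of quality of life that the article plans. If the plan stands, the analyst has two options. One is to drop the comparison without explanation. The other is to enter the same score under both protocols, which makes every difference zero and could be reported as equal quality of life. Neither tells the reader anything about the two protocols.

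**Working it through.** No sample size or power figure is involved. The check compares what the test needs with what the described data collection yields.

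**What the test needs.** For patient *i* at a given visit, the signed-rank test ranks

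d_i = DLQI_i(C-PDT) − DLQI_i(P-PDT).

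This takes two scores per patient per visit, each attributable to one protocol.

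**What V1 yields (Study Schema).**

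| Moment at V1 | Pain | DLQI |
|---|---|---|
| After P-PDT, before C-PDT | rated | none described |
| After C-PDT, both protocols given | rated | completed |
| Scores per patient | 2 | 1 |
| Scores attributable to one protocol | 2 | 0 |

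The same paragraph treats the two measures differently. Pain has a rating after each protocol. The DLQI appears only at the end, when both exposures have occurred.

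**What later visits yield.** At V2, V3 and V4 the text describes the DLQI as completed by the patient, with no mention of area. By then every patient has had both protocols. V3bis repeats the V1 procedure, so as described it gives no single-protocol score either.

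**Patients available (Population Study).** 46 patients were treated, and all were evaluated at 3 months. Of the 19 who needed retreatment one dropped out: 19 − 1 = 18 at V3bis. At 6 months, 46 − 1 = 45 completed.

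| Visit | Patients | DLQI scores per patient, as described | Needed | Pairs |
|---|---|---|---|---|
| V1 | 46 | 1 | 2 | 0 |
| V2 | number not stated | 1 | 2 | 0 |
| V3 | 46 | 1 | 2 | 0 |
| V3bis | 18 | 1 | 2 | 0 |
| V4 | 45 | 1 | 2 | 0 |

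**Could the comparison be built another way?**

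- *Between patients:* no. Randomization decides which area gets which protocol, and no patient is assigned to one protocol only.
- *Across visits:* no. No visit falls between P-PDT and C-PDT, so no change over time isolates one of them. Table 1 schedules no DLQI at screening and the V1 score follows treatment, so no pre-treatment score is described.

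**The case against.** The strongest reply is that the article nowhere says one DLQI was taken per visit. Study Schema says when the questionnaire was completed, not how its answers were laid out. Completion after C-PDT does not rule out separate answers for each area, and choosing a paired test suggests that someone expected scores for each protocol. Form layout is also the kind of detail that a condensed article leaves to the full protocol.

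Part of this stands. The single DLQI per visit is an inference. Table 1 cannot settle it: the DLQI has one row and one tick per visit, but pain also has one row and one tick at V1 and was rated twice. A reader might take that single row as proof. It is not, and the inference rests on the Study Schema text and the absence of any area-specific version in the outcome definition.

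A reader might also infer that the trial is known to hold no valid DLQI pair in any of the 46 patients at every visit. The article does not report what was collected, and 46 is the wrong denominator for V3bis and V4. The supportable statement is that there are no pairs as the collection is described.

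What does not stand is the appeal to detail held elsewhere. The article itself fixes the outcome, the two arms and the test, and no further specification can make two scores out of one whole-patient score. If area-specific answers do exist, the point becomes one of interpretation: both areas are on the same head and were treated the same day.

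**Conclusion.** The DLQI comparison is wrong as written. On the natural reading of Study Schema, no score is attributable to one protocol and the signed-rank test has no pairs at any visit. This rests on one assumption, that a single whole-patient DLQI was completed per visit. The text supports it well but does not state it.

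The severity is moderate. A reader might infer that the trial's main conclusion or its tolerability comparison is compromised, and the document does not support that. The DLQI does not enter the noninferiority decision or the sample size. Pain is rated after each protocol, and the cosmetic outcome can in principle be scored for each area, so the defect is specific to the DLQI. Nor is the lack of a pre-treatment DLQI a separate error: no change-from-baseline analysis is planned. It matters only for how the V1 score is labelled and read.

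**What to change.** In Statistical Analysis of the Secondary Outcomes, take the DLQI out of the signed-rank sentence and leave the cosmetic outcomes there. Replace it with a descriptive patient-level summary of the DLQI at V1, V2, V3, V3bis (where applicable) and V4, without attribution to either protocol, and note that the V1 score was taken after treatment. Use each visit's own denominator.

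Rest any patient-reported claim about one protocol against the other on measures recorded for each protocol, such as pain.

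Keep a between-protocol DLQI comparison only if an area-specific version was actually collected. In that case describe the instrument and how it was administered, and state that both areas are on the same head and were treated the same day, so answers may not separate the two protocols cleanly.

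The cost is a change to one sentence and the loss of one secondary comparison that, as described, has no data to support it. Analysis was still ongoing when the article was published, and the change needs no new data.

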### Data Management

All patient data were collected using an electronic case report form according to Good Clinical Practice and Standard Operating Procedures. Data collection was regularly monitored by a clinical research associate. Any deviation from the protocol was noted and the reason for the deviation documented. Any data inconsistency was brought to the attention of the clinical team and investigational site personnel (if required, data queries were sent). Resolutions to these data inconsistencies were reflected in the database.

## Results

### Population Study

The recruitment is closed and the clinical investigations are complete (Figure 2). Of the 47 recruited patients, 1 withdrew consent and did not receive any treatment protocol. A total of 46 patients were, therefore, treated with P-PDT on 1 area (for a total of 285 AK) and with C-PDT on the contralateral area (for a total of 285 AK). All these patients were evaluated at 3 months. Due to recurrent AK, 19 patients were required to undergo a second treatment visit. One of these patients dropped out because of fear of pain as intense as that experienced with C-PDT during the first treatment visit. As a result, 18 patients were retreated and 45 patients completed the study at 6 months.

All treated patients were men, and their mean age was 72.2 years. A total of 63% (29/46) of these patients had a Fitzpatrick skin type of II (Table 2). Whatever the protocol, approximately 45% of the AK were grade I and 55% were grade II (Table 3).

**Figure 2 figure2:**
[figure not shown]
Study flow diagram. V1: first treatment visit; V2: first evaluation visit; V3: second treatment visit; V3bis in case of recurrent actinic keratosis: second treatment visit; V4: third treatment visit.

**Table 2 table2:** Demographics and clinical characteristics of the 46 treated patients.

Patients characteristics		Values
Age (years), mean (SD)		72.2 (9.1)
**Sex, n (%)**		
	Male	46 (100)
	Female	0 (0)
**Fitzpatrick skin phototype, n (%)**		
	I	8 (17)
	II	29 (63)
	III	8 (17)
	IV	1 (2)

**Table 3 table3:** Lesions characteristics according to the protocol applied.

Lesions characteristics		Photodynamic therapy using the conventional protocol (N=285 AK^a^), n (%)	Photodynamic therapy using the Phosistos protocol (N=285 AK), n (%)
**Grade of lesions**				
	Grade I	130 (45.6)	128 (44.9)
	Grade II	155 (54.4)	157 (55.1)

^a^AK: actinic keratosis.

### Data Analysis

Data analysis is ongoing, and statistical results are expected to be available in the first half of 2019.

## Discussion

C-PDT that has been proven to be effective in many studies [9-11] is likely the most widely used approved protocol in Europe for PDT of AK. The major adverse effect of C-PDT is pain during treatment, which has been described as a burning and stinging sensation localized to the treatment area [24-26].

Several studies have recently shown that the Europe-approved D-PDT is as effective as C-PDT but better tolerated and nearly painless [18,27]. This painless characteristic comes from the short MAL incubation, which results in a continuous activation of small amounts of PpIX. Unfortunately, PDT using daylight activation depends on weather conditions [19] and cannot be performed in rainy, windy, or cold conditions unless a greenhouse is used [28]. Moreover, because of the varying intensity of daylight depending on the weather conditions and the locations, it is impossible to control the light dose.

New PDT protocols including the Flexitheralight protocol [20,21] have been designed to be as effective as C-PDT, as nearly painless as D-PDT, usable all year round, and associated with a known light dose. Consisting of a 30-min incubation with MAL followed by 2.5 hours of activation with a quite cumbersome, light-emitting, fabric-based device, which delivers 37 J/cm^2^ at an irradiance of 12.3 mW/cm^2^, the Flexitheralight protocol has been shown to be noninferior to C-PDT while being nearly pain-free [21]. We have revised downward the irradiation parameters of the Flexitheralight protocol: the new version of the Flexitheralight protocol, referred to as P-PDT, involves an irradiance of 1.3 mW/cm^2^ and a light dose of 12 J/cm^2^. The choice of such a light dose was based on a study that demonstrated the ability of 2 light sources with light doses lower than 15 J/cm^2^ to completely photobleach PpIX [28]. Regarding the irradiance, the value of 1.3 mW/cm^2^ was selected based on the study by Ibbotson and Ferguson, which reported effective PDT treatment when using a 7 mW/cm^2^ red light source [29]. These choices are in line with studies reporting similar efficacy for different irradiances [30] and light doses [22]. With these new irradiation parameters, the light-emitting, fabric-based device has been significantly modified to be more user friendly in terms of dimensions and ergonomics.

This study aims to assess the noninferiority in efficacy at 3 months (primary objective) and superiority in tolerability (secondary objective) of P-PDT compared with C-PDT in the treatment of AK of the forehead and scalp.

Data collection is completed, and data analysis is ongoing. The results are expected in the first half of 2019. In case of a positive assessment, P-PDT could be preferred to the conventionally used C-PDT. Moreover, as P-PDT can be performed in all weather conditions, in any geographic location, and year-round, it could also be preferred to D-PDT. Hence, P-PDT could become the treatment of choice for AK. Furthermore, an ambulatory version of P-PDT could be further investigated.

## Abbreviations

AK: actinic keratosis
ALA: 5-aminolevulinic acid
C-PDT: photodynamic therapy using the conventional protocol
CPP: Comités de Protection des Personnes (the French Ethics Committee)
D-PDT: photodynamic therapy using the daylight European consensus protocol
MAL: methyl aminolevulinate
PDT: photodynamic therapy
P-PDT: photodynamic therapy using the Phosistos protocol
PpIX: protoporphyrin IX
SCC: squamous cell carcinoma
